### Intervention

A MS-specialized neurologist examines the cognitive and physical status of the MS patient using standardized assessments like the Symbol Digit Modalities Test (SDMT) [6], Expanded Disability Status Scale (EDSS) [7], 9-Hole Peg Test (9-HPT), and Timed 25-Foot Walk (T25-FW) of the Multiple Sclerosis Functional Composite (MSFC) [8–10] every six months. Additionally, as part of a quarterly consultation on health, affective, and participation status, the neurologist examines health-associated participation and workability. The quarterly medical consultation by the neurologist includes participation-, deficit- and resource-oriented therapy planning as well as progress monitoring with regard to health-associated participation and the preservation of the working ability. In addition, it serves to ensure the stabilization of the current treatment success and the optimization or adaptation of the therapy.

As a result, the neurologist identifies risks that influence health status, workability status, family status, and social status due to the living environment. Together with the patient, the physician discusses possible treatment options to improve health and prevent workability as well as plans therapy. The neurologist initiates and coordinates the interventions with other health care providers (e.g. occupational physician, psychologist, rehabilitation physician, pension insurance, health insurance company) based on the patient’s needs. After the intervention has taken place, or if additional treatment needs have been identified by the service providers during the intervention, the neurologist and the corresponding service provider can hold a teleconsiliary discussion on the findings to ensure the success of the treatment and to discuss the therapy goal. If the neurologist identifies an acute risk of incapacity or reduction in earning capacity during his*her examination, he*she can initiate a case conference together with the other players involved to discuss possible treatment options for acutely avoiding incapacity and loss of participation. The patient can be included in the case conference to ensure treatment adherence.

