### Outcomes

#### Primary outcome

The primary outcome is the number of MS-associated sick leave days at 12- and 24-month follow-ups. These data will be provided by the routine data of the health insurance funds. In addition, the days of incapacity to work will be collected with a baseline and follow-up patient questionnaire every six months, as well as via the digital patient file during the quarterly consultations (intervention group) or the functional assessments (control group). Self-reported primary data can be used for the analysis of patients with and without secondary data from the health insurance funds (inclusion via managed care contract or treatment contract), but are somewhat more susceptible to information bias in direct comparison (e.g. self-reporting bias, recall bias) [11].

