
Additionally, primary data collected as part of the intervention at neurological practices will also be used for the evaluation as secondary outcomes:(10)The cognitive status is assessed by the Symbol Digit Modalities Test (SDMT) at baseline and on 6-, 12-, 18- and 24-month follow-up.(11)The physical status is measured using the Expanded Disability Status Scale (EDSS), the 9-Hole Peg Test (9-HPT), and the Timed 25-Foot Walk (T25-FW) of the Multiple Sclerosis Functional Composite (MSFC) at baseline and on 6-, 12-, 18- and 24-month follow-up.

Secondary data of the patients are made available by the participating health insurance companies and consists of the following:(12)Treatment costs and frequency: For each included patient, the data set contains the cost data on inpatient and outpatient care, and if applicable rehabilitation costs, medication, remedies (e.g. physiotherapy, occupational therapy), and aids as well as other payments. In addition, the GWQ Service Plus on behalf of the health insurance companies directly involved forms a match from their patient data of patients with MS that is as structurally identical as possible (propensity score matching by age, gender, 3-st. postcode, among other things), who are not included in the study. This quasi-experimental cohort study design allows further comparison between MS patients, with and without study participation, meaning between patients with and without receiving intervention services.(13)Sick leave days and sickness allowance: The data set contains the sick leave days and the paid sickness allowance for each included patient. This is the basis for calculating the short- and long-term social costs of the incapacity to work due to MS.

If these secondary data are not available, or not available to a sufficient extent, the frequency of visits to specialists, inpatient facilities, and other medical service providers can be determined from the results of the patient questionnaire.

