Additionally, the intervention’s implementation potential into the standard care system will be examined, because even if it can be demonstrated that patients benefit from the new form of care, this alone is no guarantee that it will be adopted as standard care. In that way the implementation potential is assessed through:(14)Interviews and surveys with service providers (e.g. doctors, psychologists, nurses, medical assistants) on the acceptance of the intervention. This analysis aims to record supporting and hindering factors during the project period as a secondary outcome because the knowledge of these factors is a basic prerequisite for the subsequent implementation in regular care.(15)Intervention costs: For the study period the individual interventions are remunerated to the service providers at flat rates. Based on time records and surveys, the actual costs of the individual interventions are determined to examine whether the compensatory allowances when transferred to standard care will ensure adequate future financing for the service providers even after the project duration.

The patients’ primary and secondary data are linked via a patient pseudonym. For this purpose, a trustee agency is involved.

Endpoints, outcomes, sources, and follow-ups are presented in detail in Table 2.

**Table 2 Tab2:** Endpoints, outcomes, sources, and follow-ups

	Outcome	Measurement instrument or data source	Follow-ups
PRIMARY	Number of sick leave days	Routine data from the SHI funds Patient questionnaire and digital patient health record	-^*)^ Month 0, 6, 12, 18, 24 (and during quarterly consultations)
SECONDARY	Costs of the incapacity to work	Routine data from the SHI funds Human capital or friction costs approach based on primary data for sick leave days	-^*)^ Month 0, 6, 12, 18, 24 (and during quarterly consultations)
	Treatment costs/ frequency: • Inpatient care • Outpatient care • Rehabilitation • Medication • Remedies • Therapeutic appliances • Others	Routine data from the SHI funds Patient questionnaire	-^*)^ Month 0, 6, 12, 18, 24
	Out-of-pocket payments	Patient questionnaire	Month 0, 6, 12, 18, 24
	Implementation potential into standard care: • Acceptance • Intervention costs	Interviews and survey of service providers Process analysis, time records and surveys	Study month 24 & 36 Study month 12–36

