## Discussion

To the best of our knowledge, this is the first study to consider multidisciplinary care in MS patients and its effects on health, gainful employment, and sick leave in Germany. In the project, patients with MS receive a bundle of interventions aiming to positively influence their ability to work and to participate in a self-determined life. The neurologist at the centre of the newly established network coordinates the care services offered by various service providers and, for the first time, works together with a preventive occupational physician. Tele-consultations and case discussions support this cooperation.

This complex intervention needs a highly integrated collaborative evaluation of health and health economic effects. In that way, primary and secondary data will be primarily matched, but due to the extensive collection of primary data within the project, a comprehensive evaluation of the new intervention is possible even in the absence of secondary data. The patient questionnaire and the documentation of MS-specific days of incapacity to work by the treating neurologists within the digital patient file make sufficient data available to analyze the primary endpoint, costs of incapacity to work and the course of treatment independently.

Complementing the patient perspective and the social and occupational participation outcomes achieved through the interventions, the perspective of service providers is also highlighted. Even though the new and comprehensive care for MS patients with the managing neurologist in the middle of the network can be understood as an innovation that goes beyond the current level of care. It is therefore of central importance that the new form of care is seen as useful and reasonable by the providers on the one hand, and that adequate financing can be ensured in the future on the other. The determination of the actual costs is thus indispensable for the transfer of this pilot implementation within the framework of MSnetWork.

Against this background, the study aims to improve the current employment situation of MS patients, considering disease-specific, therapeutic, psychosocial, and socioeconomic factors and the providers’ perspective to ensure such future treatment for MS patients.

If the project proves to be a success, a transfer for the treatment of other chronic diseases with an impact on the ability to work is conceivable and desirable.

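### One of the three sources for sick leave days, the digital patient file, is filled quarterly in the intervention arm but six-monthly in the control arm, so it should not determine the 12-month comparison

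*Protocol article*

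**What the plan says.** The Primary outcome section names health-insurance routine data first. It then adds a patient questionnaire at baseline and every six months, and entries made "via the digital patient file during the quarterly consultations (intervention group) or the functional assessments (control group". On the use of these data it says: "Self-reported primary data can be used for the analysis of patients with and without secondary data from the health insurance funds". It concedes that self-report is more open to information bias, but only as a general weakness.

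The timing of the functional assessments is given twice. The Intervention section has the tests, including those "of the Multiple Sclerosis Functional Composite (MSFC) [8–10] every six months". The Secondary outcomes section schedules the cognitive and physical tests "at baseline and on 6-, 12-, 18- and 24-month follow-up", without distinguishing the arms.

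Table 2 lists "Patient questionnaire and digital patient health record" as a source of the primary outcome beside claims data. Its cost-of-incapacity row also draws on primary sick-leave data with the same timing, quarterly consultations included.

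On who records, the Discussion says that the questionnaire together with "the documentation of MS-specific days of incapacity to work by the treating neurologists within the digital patient file make sufficient data available" for analysing the primary endpoint. On that clinician's role, the Intervention section says: "The neurologist initiates and coordinates the interventions with other health care providers".

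The recruitment section allows enrolment by a direct treatment contract with no health insurer involved. The Control condition section gives control patients the intervention after month 12, at the same frequency as the intervention group.

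**The concern.** A randomised comparison is protected only if the outcome is ascertained in the same way in both arms. Here one listed source is not. A three-month look-back with four prompts can capture a different share of true sick leave days than a six-month look-back with two, even if the intervention does nothing. The person recording also knows the arm, and because the outcome is restricted to MS-associated days, an entry can involve a judgement about cause.

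An error of this kind shifts the estimated difference itself. Intention-to-treat analysis does not remove it, and a larger sample only estimates the shifted value more precisely. The article's remark on recall bias does not mention that, for the file, its own schedule makes the recall period depend on the arm.

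**Working it through.** **1. Collection by source in months 1–12.** This is a comparison of statements; the article gives no figure to reproduce.

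| Source | Intervention arm | Control arm | Same in both arms? |
|---|---|---|---|
| Claims data | continuous | continuous | yes |
| Questionnaire | months 6, 12 | months 6, 12 | yes |
| Digital file | months 3, 6, 9, 12 | months 6, 12 | no |

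The file is therefore scheduled for 12/3 = 4 entries against 12/6 = 2 after baseline. In months 13–24 it is 4 against 4. Within the control arm it goes from 2 entries in the first period to 4 in the second, so the pre-post comparison described under Study design would see a change in recording at the same moment as the start of the intervention.

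**2. Scale if the file were the only source.** Inputs from the Sample size section: mean 25 days, planned difference 5 days (so 20 in the intervention arm), 80% power, two-sided 0.05. The relative recording gap u between arms is an assumption; the documents give none.

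- Gap applied to the 25-day mean: 0.10 × 25 = 2.5 and 0.20 × 25 = 5 days.
- Gap applied to the 20-day mean: 0.10 × 20 = 2 and 0.20 × 20 = 4 days.
- Range: about 2–5 days, or 40–100% of the planned 5.

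**3. Scale if the file served a fraction f of patients.** Shift = f × (2 to 5 days). With an assumed f = 20% this is 0.4–1.0 days; with f = 0 it is nil. The documents do not give f.

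**4. Effect on power, for illustration.** This uses a normal approximation to a difference in means, not the planned zero-inflated model. The SD implied by 80% power is 5 × √(N/4) / (1.96 + 0.84), which is 21.9 for net N = 600 and 26.2 for net N = 860. Power at an observed difference d is then Φ(2.80 × d/5 − 1.96), the same for both N. If the control file misses a share u more days, d = 25(1 − u) − 20.

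| u | d (days) | Power |
|---|---|---|
| 0% | 5 | 80% |
| 5% | 3.75 | 56% |
| 10% | 2.5 | 29% |
| 15% | 1.25 | 10% |
| 20% | 0 | 2.5% |

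In the opposite direction, suppose there is no true effect and the intervention file records 5%, 10% or 20% fewer of 25 days. The spurious difference is then 1.25, 2.5 or 5 days, and the two-sided test rejects in about 11%, 29% or 80% of trials.

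**The case against.** A reader might infer that the primary outcome as a whole is measured differently by arm. The article does not support that. Claims data are named first and recorded continuously, the questionnaire is six-monthly for everyone, and the file is introduced as an addition.

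A reader might also infer that the plan accepts the file alone as enough for the endpoint. The Discussion claims sufficiency for questionnaire and file together, and the questionnaire is symmetric. Nor is the lack of a detailed rule for conflicting or missing sources a fault in itself: such a rule commonly sits in the full protocol or analysis plan, which are not shown, and the text already leans towards claims first.

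It is also fair to say that no bias of known sign has been shown. More frequent prompting would probably record more days in the intervention arm and work against the intervention. Recording by a clinician who knows the arm could favour it, but nothing says that this happens. The 2–5 day range is an assumed worst case with the file as the only source for every patient.

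All of this limits the point without removing it. The arm-specific schedule is stated, the file is a listed source for the primary outcome, and primary data are permitted for patients with and without claims.

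**Conclusion.** The point holds for the digital file only. In the 12-month parallel comparison, one of three listed sources has a look-back that differs by arm (three against six months), with entries made by a clinician whose role reveals the allocation. It affects the primary result only to the extent that file entries determine a patient's count, most plausibly in those enrolled without an insurer. That share, the recording gap and its direction are all unknown. On the assumed 10–20% gap the shift is at most about 2–5 days against the planned 5, scaled down by the fraction of patients served by the file.

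The control arm's pre-post comparison has the same weakness, because its contact frequency rises after month 12. Costs of incapacity inherit it wherever they are built on file entries. This is an inexpensive improvement to the plan, not evidence that the trial's primary comparison is biased.

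**What to change.** State that the primary endpoint uses claims data wherever they are available and, where they are not, the six-monthly questionnaire in both arms. State that quarterly file entries determine neither the primary nor the cost-of-incapacity endpoint, and use the file only in a sensitivity analysis. Apply the same source rule to the control arm's pre-post comparison.

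Restricting the file to its month 6 and month 12 entries would equalise recording only if those entries covered six months in both arms, so it is not a simple substitute for the questionnaire.

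The cost is a few sentences in the analysis plan and some file entries left out of the main analysis; both symmetric sources are already being collected. The questionnaire remains self-report by patients who probably know their arm. The change equalises timing and takes the recording away from the treating neurologist, but it does not remove that limitation.

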#### Secondary outcomes

The secondary outcomes include primary data collected within the evaluation study and secondary data provided by the health insurance funds. For patients, primary data will be collected by a questionnaire at baseline and on 6-, 12-, 18-, and 24-month follow-up, that consist of the following:Health-related quality of life is measured by the German version of the Multiple Sclerosis Quality of Life (MSQoL)-54 instrument [12], a diagnosis-specific MS questionnaire. It contains 52 items distributed into 12 scales, and two single items. In addition to the generic quality of life items retrieved from the SF-36, the questionnaire captures health aspects that are particularly significant for MS patients (18 items in the areas of health distress, sexual function, satisfaction with sexual function, overall quality of life, cognitive function, energy, pain, and social function).The EQ-5D-5L is a preference-based HRQoL measure and is used to evaluate the generic quality of life. The EQ-5D-5L contains one item for each of the five dimensions mobility, self-care, usual activities, pain/discomfort, and anxiety/depression. The answers given to EQ-5D-5L can be converted into a utility score, the EQ-5D index. Additionally, the EQ-5D-5L includes a Visual Analog Scale (VAS), ranging from 0 (the worst possible health status) to 100 (the best possible health status) [13]Affective status is evaluated by the short form of the Depression, Anxiety and Stress Scale (DASS) [14, 15]. The DASS comprises three subscales each consisting of 7 items: depression, anxiety, and stress.Fatigue as a common symptom in MS patients [16] is measured with the Fatigue Scale for Motor and Cognitive Functions (FSMC] [17]. The 20-item scale contains cognitive and motor subscales with 10 items each.A short scale measuring the subjective prognosis of gainful employment (SPE-scale) [18] is used to assess the likelihood of reduction of work capacity (3 Items).Patients’ adherence to therapy and treatment is measured by the Adherence Assessment Questionnaire (AAQ) [19]. The AAQ consists of 11 items, including a visual analog scale.Self-efficacy is carried out with the 13-item short form of the Coping Self-Efficacy Scale (CSES) [20]. The CSES measures one’s confidence in performing coping effectively with life challenges e.g. due to chronic illness and it can assess changes in coping self-efficacy (CSE) over time in intervention research.The level of patient satisfaction with the new intervention is measured with an adapted version of the Patient Satisfaction Questionnaire (ZUF-8) [21, 22] The original version was adapted for use in outpatient care.Out-of-pocket payments by households due to the MS disease are measured with 16 items. These include co-payments, monetary transport costs, and time losses. The items are based on the Multiple Sclerosis Health Resource Utilization Survey [23] but were adapted for the specific research design in MSnetWork.

Additionally, primary data collected as part of the intervention at neurological practices will also be used for the evaluation as secondary outcomes:(10)The cognitive status is assessed by the Symbol Digit Modalities Test (SDMT) at baseline and on 6-, 12-, 18- and 24-month follow-up.(11)The physical status is measured using the Expanded Disability Status Scale (EDSS), the 9-Hole Peg Test (9-HPT), and the Timed 25-Foot Walk (T25-FW) of the Multiple Sclerosis Functional Composite (MSFC) at baseline and on 6-, 12-, 18- and 24-month follow-up.

Secondary data of the patients are made available by the participating health insurance companies and consists of the following:(12)Treatment costs and frequency: For each included patient, the data set contains the cost data on inpatient and outpatient care, and if applicable rehabilitation costs, medication, remedies (e.g. physiotherapy, occupational therapy), and aids as well as other payments. In addition, the GWQ Service Plus on behalf of the health insurance companies directly involved forms a match from their patient data of patients with MS that is as structurally identical as possible (propensity score matching by age, gender, 3-st. postcode, among other things), who are not included in the study. This quasi-experimental cohort study design allows further comparison between MS patients, with and without study participation, meaning between patients with and without receiving intervention services.(13)Sick leave days and sickness allowance: The data set contains the sick leave days and the paid sickness allowance for each included patient. This is the basis for calculating the short- and long-term social costs of the incapacity to work due to MS.

If these secondary data are not available, or not available to a sufficient extent, the frequency of visits to specialists, inpatient facilities, and other medical service providers can be determined from the results of the patient questionnaire.

Additionally, the intervention’s implementation potential into the standard care system will be examined, because even if it can be demonstrated that patients benefit from the new form of care, this alone is no guarantee that it will be adopted as standard care. In that way the implementation potential is assessed through:(14)Interviews and surveys with service providers (e.g. doctors, psychologists, nurses, medical assistants) on the acceptance of the intervention. This analysis aims to record supporting and hindering factors during the project period as a secondary outcome because the knowledge of these factors is a basic prerequisite for the subsequent implementation in regular care.(15)Intervention costs: For the study period the individual interventions are remunerated to the service providers at flat rates. Based on time records and surveys, the actual costs of the individual interventions are determined to examine whether the compensatory allowances when transferred to standard care will ensure adequate future financing for the service providers even after the project duration.

The patients’ primary and secondary data are linked via a patient pseudonym. For this purpose, a trustee agency is involved.

Endpoints, outcomes, sources, and follow-ups are presented in detail in Table 2.

**Table 2 Tab2:** Endpoints, outcomes, sources, and follow-ups

	Outcome	Measurement instrument or data source	Follow-ups
PRIMARY	Number of sick leave days	Routine data from the SHI funds Patient questionnaire and digital patient health record	-^*)^ Month 0, 6, 12, 18, 24 (and during quarterly consultations)
SECONDARY	Costs of the incapacity to work	Routine data from the SHI funds Human capital or friction costs approach based on primary data for sick leave days	-^*)^ Month 0, 6, 12, 18, 24 (and during quarterly consultations)
	Treatment costs/ frequency: • Inpatient care • Outpatient care • Rehabilitation • Medication • Remedies • Therapeutic appliances • Others	Routine data from the SHI funds Patient questionnaire	-^*)^ Month 0, 6, 12, 18, 24
	Out-of-pocket payments	Patient questionnaire	Month 0, 6, 12, 18, 24
	Implementation potential into standard care: • Acceptance • Intervention costs	Interviews and survey of service providers Process analysis, time records and surveys	Study month 24 & 36 Study month 12–36
	Reduction in earning capacity: •Subjective prognosis of gainful employment • Employment situation	Subjective prognosis of gainful employment scale (SPE) Patient questionnaire	Month 0, 12, 24 Month 0, 12, 24
	Physical status	Expanded Disability Status Scale (EDSS) Multiple Sclerosis Functional Composite (MSFC: T25-FW, 9-HPT)	Month 0, 6, 12, 18, 24
	Cognitive status Affective status Fatigue	Symbol Digit Modalities Test (SDMT) Depressions-Anxiety-Stress-Scale (DASS) Fatigue Scale for Motor and Cognitive Functions (FSMC)	Month 0, 6, 12, 18, 24
	Health-related quality of life	Multiple Sclerosis Quality of Life (MSQoL)-54 instrument EuroQol-questionnaire (EQ-5D-5L)	Month 0, 6, 12, 18, 24
	Patients’ adherence to therapy	Adherence Assessment Questionnaire (AAQ)	Month 0, 6, 12, 18, 24
	Self-Efficacy	Coping Self-Efficacy Scale (CSES)	Month 0, 6, 12, 18, 24
	Patient satisfaction with the new intervention	Client Satisfaction Questionnaire (ZUF-8)	Month 12, 24

*) Continuous recording within the claims data of the statutory health insurers

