### Subjects and eligibility criteria

Criteria for study inclusion comprise the following: (1) patients with a confirmed diagnosis of multiple sclerosis; (2) patients of working age (aged 18–65 years); (3) patients employed (part-time or full-time) or in study or vocational training.

Criteria for study exclusion comprise the following: (1) patients with MS who are no longer of working age (older than 65 years); (2) patients who are unable to work; (3) patients with severe impairment of independence (corresponds to care level 4 and 5 in German social law), and (4) patients with severe mental disorders.

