### Control condition

In the first 12 month, participants in the control group will not receive trial-related healthcare interventions, but “treatment as usual”, i.e. the standard healthcare as currently applied in the MS standard treatment in Germany. This comparator was chosen because the research question is whether the new intervention affects outcomes like days of incapacity of work, quality of life, and cost-effectiveness and for this a comparison to “usual care” is warranted.

However, patients in the control group do also receive interventions after 12 months at the same frequency as participants in the intervention group (Fig. 2).

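### The matched-cohort comparison equates taking part in the study with receiving the intervention, which is untrue for half the participants in months 0–12

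*Protocol article*

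**What the plan says.** Secondary outcomes, item (12), Treatment costs and frequency, describes claims data for all participants, with no limit to one arm: "For each included patient, the data set contains the cost data on inpatient and outpatient care". A comparison cohort is drawn from the insurers' MS patients outside the study, by "propensity score matching by age, gender, 3-st. postcode, among other things". The purpose is then stated: "This quasi-experimental cohort study design allows further comparison between MS patients", those in the study against those outside it, "meaning between patients with and without receiving intervention services".

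Study design sets 1:1 allocation and 24 months of participation, with the control group on standard care for 12 months and on the intervention afterwards. Control condition confirms this: "In the first 12 month, participants in the control group will not receive trial-related healthcare interventions". Sample size gives 950 planned participants, 475 per group.

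**The concern.** The comparison in item (12) treats two distinctions as one. Being in the study and receiving its services coincide only in months 13–24. In months 0–12 the control group is in the study and receives none of the trial's services. The sentence therefore misdescribes the contrast for that year, and an analysis that followed it would place untreated patients on the treated side.

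Two things are at stake. First, the estimate would be diluted by a known factor. Second, the same number would contain any difference between people who join the trial and people who do not, and with the arms pooled the reader could not tell the two apart. The comparison sits under treatment costs, and Statistical analyses plans to set intervention costs against saved costs. A mislabelled contrast could therefore be read as evidence on savings.

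**Working it through.** **Inputs.** Planned total 950 and 475 per group (Sample size). Allocation 1:1, 24 months of participation, control group untreated by the trial in months 0–12 and treated in months 13–24 (Study design, Control condition). The article states no figure for the matched comparison itself.

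**The plan's own figure.** 950 / 2 = 475 per group, as stated.

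**Exposed share if all participants form the study side** (person-months, planned numbers, before dropout):

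| Period | Intervention group | Control group | Exposed / total | Share |
|---|---|---|---|---|
| Months 0–12 | 475 × 12 = 5,700 | 0 | 5,700 / 11,400 | 50% |
| Months 13–24 | 5,700 | 5,700 | 11,400 / 11,400 | 100% |
| All 24 months | 11,400 | 5,700 | 17,100 / 22,800 | 75% |

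**What each contrast estimates.** Let D be a constant additive effect on mean cost or use while exposed. Let b be the difference between participants and their matches that would exist without any intervention (selection, or an effect of taking part). Then:

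- all participants vs matches, year 1: 0.5 × D + b
- all participants vs matches, months 13–24: D + b
- all participants vs matches, 24 months: 0.75 × D + b
- intervention group vs its matches, year 1: D + b
- control group vs its matches, year 1: b

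The first line has two unknowns and one observed number, so D and b cannot be recovered from it. Splitting by arm yields b directly, because neither the year-1 control group nor its matches receive the trial's services. Subtracting the last line from the one above it gives D, which is the randomized contrast. The matched cohort's distinct use is therefore in months 13–24, when no untreated randomized group remains. The year-1 value of b then shows how far that later comparison can be trusted, provided b is stable over time.

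**Precision.** Using one arm in year 1 halves the study side. At a fixed number of matches per participant and similar variance, the standard error rises by √2 ≈ 1.41. The expected effect doubles, from 0.5 × D to D, so the ratio of effect to standard error still improves by about 2 / 1.41 ≈ 1.41.

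**The case against.** The strongest reply is that pooling is inferred. The article says only that the design permits a further comparison. It gives no estimand, time window or model, and the clause could be read as defining the contrast by receipt of services, in which case nothing is diluted. Claims are recorded continuously and linked by pseudonym, so an analysis by arm and period is feasible. This stands in part: dilution is conditional on following the sentence. The sentence nevertheless equates participation with receipt, and under this design the equation is false for year 1. That is a misstatement and not detail left to another document.

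Three stronger readings are tempting, and the documents do not support them.

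- A reader might infer that healthier people join and that their advantage is credited to the intervention. Trial patients must be "patients employed (part-time or full-time) or in study or vocational training", and the named matching variables do not cover this. But the list is expressly open and aims at the closest structural match, so employment, prior sick leave or prior costs may be on it. Selection remains a risk of unknown size and sign.
- A reader might infer that the comparison underestimates the effect overall. That holds for dilution alone. With b of unknown sign, the net direction is unknown.
- A reader might translate the dilution into sick leave days or lost power using the planning difference of 5 days. That figure belongs to the randomized primary outcome, whereas the matched cohort is described under treatment costs. No cost effect or sample size is given for it, and claims data may not cover patients enrolled by direct treatment contract.

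It is also fair that the matched cohort is an add-on, openly called quasi-experimental, and is absent from the analyses of the intervention effect listed under Study design.

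**Conclusion.** The point holds as a misstatement of a supplementary comparison. Item (12) conflicts with Study design and Control condition for months 0–12. If followed as written, the comparison carries 50% of any additive effect in year 1, all of it in months 13–24, and 75% over 24 months. Selection would be mixed in and could not be separated.

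The factors rest on three assumptions: all participants are pooled, the effect is constant while exposed, and the arms stay about equal in size among patients with claims data. Randomization at patient level makes the last reasonable at the outset, but unequal dropout would shift the 50%. If the effect builds up over time, the 24-month figure changes.

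The randomized primary comparison, the long-term follow-up of the intervention group and the pre-post analysis of the control group are not touched. The correction is worth making because it changes what the matched comparison can show.

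**What to change.** 1. Drop the statement that study participation means receiving the intervention.
2. Define the study side by arm and period: intervention group only in months 0–12; either or both groups in months 13–24, stating which, since the two groups then differ in time on the intervention.
3. Report the year-1 control group against its own matches as a check on selection or participation effects. A clear difference there should limit what is concluded from the months 13–24 comparison.

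This needs a change of analysis wording and the allocation flag in the linked data, with no new data collection from patients. The cost is a smaller study side in year 1, with a standard error about 1.41 times larger under the assumptions above.
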